#### Expectations of treatment effect

At baseline, participants will be asked about their expectations of the effect they think the study treatments will have on their knee pain using a 5-point ordinal scale ranging from no effect to complete recovery.

#### Process measures

Additional process measures will be collected for both groups at 3 months for the purposes of measuring the acceptability of the interventions (rather than to determine treatment efficacy). These additional measures include: i) *appropriateness of the interventions* using a custom designed questionnaire and ii) *satisfaction with the intervention* using a 2-item custom designed questionnaire that asks about the overall satisfaction with the content and delivery of the intervention.

### Sample size

The primary endpoints of the trial are between-group (PCST + Ex group versus the educational control group) differences in change in knee pain on walking (NRS) and change in physical function (WOMAC). Moderate between-group treatment effects of around 0.5 have previously been reported for pain and function following individual exercise programs in people with knee OA [13, 67]. Therefore, to enable detection of at least a 0.5 effect size between groups in either pain or function in a two-arm trial with 80% power, a significance level at 0.05 and allowing for 15% attrition rate, we will recruit 74 participants in each group or a total of 148 participants.

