The primary objective of this pragmatic randomised controlled trial (RCT) is to evaluate whether an Internet-based intervention that combines PCST and physiotherapist-guided exercise (PCST + Ex), is more effective than online educational material (educational control) in people with persistent OA knee pain. We hypothesise that PCST + Ex will be more effective in reducing pain and improving self-reported physical function after 3 months than the educational control intervention. Secondary hypotheses are (i) the PCST + Ex will be more effective in reducing pain and improving self-reported physical function after 9 months than the educational control intervention; and (ii) there will be greater improvements in health-related quality of life and psychological outcomes, as well as a better participant-perceived response to treatment in the PCST + Ex after 3 months and 9 months than the education control intervention.

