### Outcome measures

The outcome measures are summarised in Table 3. Primary outcomes will be measured at baseline, 3 months and 9 months. Conclusions regarding treatment effectiveness will be evaluated based on changes in primary outcome measures from baseline to 3 months. Our two primary outcomes, which are recommended as valid measures of pain and physical function for knee OA [52], are:

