Strengths of this RCT study design are the pragmatic nature of treatment delivery by practising physiotherapists as well as the reproducibility of both the physiotherapy and pain coping skills programs. These features will improve the ability to translate the findings into a range of health care settings and enable future researchers to replicate the intervention. Importantly, the physiotherapy-guided home exercise program is individualised with regard to the content, and the intensity level of the exercises are individually monitored, progressed or stepped back throughout the intervention according to participant feedback. Additionally, physiotherapists will support and reinforce the participants’ use of the pain coping skills during the exercise sessions so as these skills can not only be integrated into the exercise program, but also encouraged within daily life. The inclusion of participants regardless of their geographic location will further enhance the generalisability of results. The study is adequately powered for our primary outcome measures.

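### The sample size gives each of two primary outcomes the full 0.05, and the protocol does not say whether one or both must be positive to claim effectiveness

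*Protocol article*

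**What the plan says.** The Sample size section names two primary endpoints, the between-group differences in change in walking pain (NRS) and in physical function (WOMAC). It sizes the trial "to enable detection of at least a 0.5 effect size between groups in either pain or function in a two-arm trial with 80% power", with "a significance level at 0.05 and allowing for 15% attrition rate", and arrives at 74 per group, 148 in total. One significance level is given. It is not divided between the outcomes, and its sidedness is not stated.

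Three other places bear on how the two results will be used:

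- The end of the Background words the primary hypothesis with both outcomes: "We hypothesise that PCST + Ex will be more effective in reducing pain and improving self-reported physical function after 3 months".
- Outcome measures says: "Conclusions regarding treatment effectiveness will be evaluated based on changes in primary outcome measures from baseline to 3 months". It does not say whether one positive outcome is enough or both are needed.
- The Discussion says: "The study is adequately powered for our primary outcome measures".

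The Data and statistical analysis section names the models but gives no ordering, split of alpha or joint rule for the two outcomes.

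**The concern.** With two primary outcomes, the error rate and the power of the effectiveness conclusion depend on how the two tests are combined. The sample size sentence joins the outcomes with *either* and the hypothesis joins them with *and*. The section on conclusions does not settle the matter. The single 0.05 and the single 80% describe one test, while the conclusion rests on two.

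The risk is a split result, for example pain positive and function not. Nothing in the article says whether that counts as effective. If the rule is chosen after the data are seen, the error rate of the claim is no longer the one stated.

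**Working it through.** **Inputs from the Sample size section:** standardised effect d = 0.5, power 80%, significance level 0.05, attrition 15%, 74 per group.

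**Assumptions:** two-sided tests; true effect 0.5 on both outcomes where power is computed; correlation between the two test statistics from 0 to 0.9. The protocol gives no correlation, so the range is shown.

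**Step 1. Reproduce the plan's figure.** For one outcome,

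n = 2(z₀.₉₇₅ + z₀.₈₀)²/d² = 2(1.960 + 0.842)²/0.25 = 62.8 per group.

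62.8/0.85 = 73.9, so 74. By the t-test, n = 64 per group, and 64 × 1.15 = 73.6, also 74. Other settings do not give 74:

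- one-sided 0.05 needs 50, or 59 after attrition;
- two-sided 0.025 needs 77, or 77/0.85 = 90.6, so 91.

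The number is therefore that of one outcome at the full two-sided 0.05.

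**Step 2. Power for one outcome.** Evaluable participants: 74 × 0.85 = 62.9, taken as 63 per group. The expected test statistic is 0.5 × √(63/2) = 2.81. Power is 80% at 0.05 (79.5% by the t-test) and 71% at 0.025 (70% by the t-test).

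**Step 3. Both outcomes together.** Z₁ and Z₂ are bivariate normal with correlation ρ.

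- Familywise error if either suffices at 0.05: 1 − P(|Z₁| < 1.96 and |Z₂| < 1.96), both means 0.
- Power if both are required at 0.05: P(Z₁ > 1.96 and Z₂ > 1.96), both means 2.81.
- Power for at least one outcome under Holm: 1 − P(Z₁ < 2.241 and Z₂ < 2.241), both means 2.81. Hochberg is never lower.

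| ρ | Familywise error, either at 0.05 | Power, both at 0.05 | Power, at least one, Holm |
|---|---|---|---|
| 0 | 9.75% | 64% | 92% |
| 0.3 | 9.5% | 67% | 88% |
| 0.5 | 9.1% | 69% | 85% |
| 0.7 | 8.4% | 71% | 82% |
| 0.8 | 7.8% | 73% | 80% |
| 0.9 | 7.0% | 75% | 77% |

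Checks at ρ = 0: 1 − 0.95² = 0.0975; 0.801² = 0.642; 1 − (1 − 0.714)² = 0.918.

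The error column counts false positives in both directions. In favour of the intervention alone it runs from 4.9% (ρ = 0) to 3.5% (ρ = 0.9), against 2.5% for one test.

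**Step 4. Is 74 an at-least-one calculation?** No. With 63 evaluable and each outcome at 0.05, the power for at least one positive outcome is 96% at ρ = 0 and 85% at ρ = 0.9, above the stated 80% throughout.

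**The case against.** The strongest reply is that the protocol states no success rule based on either outcome. *Either* appears only in a sentence about power, where its ordinary sense is that 74 per group gives 80% power for whichever outcome is considered. Steps 1 and 4 support that reading. The hypothesis names two expected benefits and need not be a joint test. If the outcomes are reported one by one, all four passages are compatible, and the Discussion's claim of adequate power holds for each outcome separately. The statistical analysis plan is not shown and may contain a multiplicity procedure.

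Most of this stands. A reader might infer that the protocol contradicts itself, with an *either* rule in one place and an *and* rule in another, and that the trial must therefore have an inflated error or less than 80% power. The documents do not support that. No formal rule of either kind is written, and Outcome measures does not demand that both be positive. The two alternatives are also not exhaustive: Holm or Hochberg holds 5% at the same sample size and, if both effects are 0.5, keeps at-least-one power at 80% or more up to a correlation of 0.8.

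The power under a both-required rule also depends on the model. The planned analysis adjusts for baseline. If 0.5 is standardised to the unadjusted SD at follow-up, the test statistic grows by 1/√(1 − r²), where r is the baseline-to-follow-up correlation. With ρ from 0 to 0.9, power for both would then be about 75–83% at r = 0.4 and 81–87% at r = 0.5. Both values of r are assumptions; the Sample size section takes no credit for adjustment and gives no such correlation.

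One part of the reply does not stand. The absence of a multiplicity procedure would be no finding by itself, but here the document fixes the number of participants at unadjusted 0.05 for two outcomes that jointly carry the conclusion. A later plan could set a rule. The stated 80% would then describe neither a both-required rule nor one outcome tested at 0.025.

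**Conclusion.** The point holds as a badly fixed alpha and an unstated decision rule, not as an arithmetic error or a proven contradiction. The 74 per group is sound for one outcome at two-sided 0.05, and 80% power per outcome is a fair description of it. What the article lacks is the link from two such tests to one conclusion.

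If either outcome at 0.05 is enough, the familywise error is about 7.0–9.75%. If both are needed, power is about 64–75%. The ranges cover assumed correlations of 0 to 0.9. The power figures also assume 15% attrition, true effects of 0.5 SD on both outcomes and no gain from baseline adjustment. Two-sided testing is inferred from the reproduced sample size. The sample size, outcomes, primary time point and model need not change.

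**What to change.** State one rule before unblinding and align the text with it.

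- **Option A.** Test the two 3-month primary outcomes with Holm or Hochberg at familywise two-sided 0.05, and claim effectiveness only for the outcome or outcomes that pass. In Sample size, restate power as about 77–92% for at least one outcome when both effects are 0.5 SD (correlation 0.9 to 0), and about 70% for one given outcome at 0.025.
- **Option B.** If effectiveness requires both outcomes, keep 0.05 for each and restate power as about 64–75%, or give the baseline correlation that justifies a higher figure.

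Under either option, bring the hypothesis in the Background, the sentence on conclusions in Outcome measures and the power statement in the Discussion into line.

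The cost is wording in the protocol and the analysis plan. No extra participants are needed. The downside is a stricter threshold for one outcome under Option A, or a less favourable stated power under Option B.

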### Data and statistical analysis

A biostatistician (MPS) blinded to group allocation will analyse data. Main comparative analyses between groups will be performed using intention-to-treat. This analysis will include all participants who have missing data and those who do not fully adhere to the protocol. Demographic characteristics, as well as baseline scores on primary and secondary outcome measures, will be inspected to assess baseline comparability of treatment groups. These variables will also be examined for those participants who withdraw from the study and those who remain. Descriptive statistics will be presented for each group as the mean change (standard deviation, 95% confidence intervals) in the outcomes from baseline to each time-point. For continuous outcomes differences in mean change will be compared between groups using linear regression random effects modelling adjusted for baseline values of the outcome. Proportional odds models will compare improvement between groups based on perceived ratings of change as well as the proportion in each group who attain the minimum clinical important difference (MCID) for pain and function. The MCID to be detected in OA trials is a change in pain of 1.8 units (out of 10) [54] and change in function of 6 points (out of 68) [57]. Model diagnostic checks will utilise residual plots. Similar regression models for binary and ordinal outcome measures will use random effects logistic and proportional odds models, respectively. We will also perform a per protocol analysis as appropriate.

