### Randomisation and allocation concealment

On completion of baseline assessment, participants will be consecutively randomised to one of two groups: 1) educational control (online educational material) or 2) intervention group (online educational material, Internet-based PCST and physiotherapy-guided exercise program delivered via the Internet). Computer generated randomisation will be conducted by random permuted blocks of size 2-8 stratified by gender (male or female) and residency (metropolitan or rural), prepared by our study biostatistician (MS). To conceal randomization, consecutively numbered, sealed, opaque envelopes will be prepared by a researcher with no other involvement in the study. The envelopes will be stored in a locked location and will be opened in sequence within each stratum to reveal group allocation.

All primary and secondary outcome data will be completed online and thus will be automatically entered into a database. By necessity, participants and physiotherapists will be unblinded to group allocation; however, participants will remain blinded to research hypotheses. The statistician will be blinded to group allocation until completion of the statistical analyses.

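### Randomisation is stratified by gender and residency, but the stated model for the continuous primary outcomes adjusts only for baseline, which may forgo a little precision

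*Protocol article*

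**What the plan says.** Under Randomisation and allocation concealment, the protocol article describes "random permuted blocks of size 2-8 stratified by gender (male or female) and residency (metropolitan or rural"), which gives 2 × 2 = 4 strata.

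Under Data and statistical analysis, it says of continuous outcomes that "differences in mean change will be compared between groups using linear regression random effects modelling adjusted for baseline values of the outcome". The baseline score is the only covariate named. The random effects are not specified, and nothing says that they represent strata. No other section brings gender, residency or stratum into an analysis model.

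The same section plans proportional odds and logistic models for perceived change and for reaching the minimum clinically important difference. It describes the models for binary and ordinal outcomes as similar to the linear ones and names no stratification factor for them either.

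The Sample size section sets the trial "to enable detection of at least a 0.5 effect size between groups in either pain or function", with 80% power, "a significance level at 0.05" and 15% attrition, giving 74 per group.

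**The concern.** Stratified blocking holds the arms close to equal on gender and residency. If those factors predict the outcome, this removes part of the chance variation in the treatment difference. A model that omits them leaves their variance in the residual, so its standard error describes a less balanced design than the one used. The reported interval is then wider than it needs to be, and the test rejects less often than its nominal level under the null.

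What is at stake is precision on the two primary outcomes. The article does state an adjustment set, and that set omits the factors that the design balanced on.

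**Working it through.** **Inputs from the Sample size section.** Effect 0.5 SD, power 80%, alpha 0.05, attrition 15%, 74 per group. The section does not state sidedness; two-sided is assumed.

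**Reproducing the sample size.** n per arm = 2(1.960 + 0.842)² / 0.5² = 62.8, so 63. Allowing for attrition, 63 / 0.85 = 74.1, which agrees with the stated 74. With 74 × 0.85 = 62.9 evaluable per arm, power is 80.1% by the normal approximation and 79.5% by the t-test. The calculation is a plain two-group comparison with no credit for adjusting for baseline or strata.

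**Effect of omitting the strata.** Let R² be the share of outcome variance, after baseline adjustment, that gender and residency explain. The document gives no value, so a range is shown. The calculation treats the 3-month comparison as a baseline-adjusted linear model, with 63 per arm, residual SD 1 and exact balance on the strata.

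- Standard error reported without strata: √(2/63) = 0.178.
- True standard error: √((1 − R²) × 2/63).
- Interval width ratio: 1/√(1 − R²).
- True alpha without strata: 2Φ(−1.96/√(1 − R²)).
- Power without strata: Φ((0.5/0.178 − 1.96)/√(1 − R²)).
- Power with strata: Φ(0.5/(0.178√(1 − R²)) − 1.96).

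For R² = 0.05, √0.95 = 0.975. The width ratio is 1/0.975 = 1.026, and alpha is 2Φ(−2.01) = 4.4%. Power is Φ(0.87) = 80.7% without the strata and Φ(0.92) = 82.1% with them.

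| Assumed R² | Interval width ratio | True alpha, strata omitted | Power, omitted | Power, included | Points forgone |
|---|---|---|---|---|---|
| 0 | 1.000 | 5.0% | 80.1% | 80.1% | 0 |
| 0.02 | 1.010 | 4.8% | 80.4% | 80.9% | 0.5 |
| 0.05 | 1.026 | 4.4% | 80.7% | 82.1% | 1.4 |
| 0.10 | 1.054 | 3.9% | 81.4% | 84.1% | 2.7 |
| 0.20 | 1.118 | 2.8% | 82.8% | 88.1% | 5.3 |

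**Check by simulation.** Each run randomised 148 participants in four strata with blocks of 2, 4, 6 or 8 and 15% random dropout. The two factors had assumed frequencies of 60% and 40%. There were 5,000 runs per setting.

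- Width ratios at an effect of 0.5 were 0.998, 1.009, 1.025, 1.052 and 1.118 for R² of 0, 0.02, 0.05, 0.10 and 0.20, close to the formula.
- Including the strata changed power by −0.1, 0.4, 2.0, 2.9 and 5.5 points.
- Type I error without the strata was 5.3%, 4.6%, 5.1%, 3.8% and 3.1%. Monte Carlo error is about √(0.05 × 0.95/5000) = 0.3 points, so small departures from 5% cannot be resolved. At R² = 0.05 the simulated 5.1% shows no conservatism, against 4.4% by formula. Dropout and unfinished blocks also loosen the exact balance that the formula assumes.
- At R² = 0, power was 78.3% without and 78.2% with the strata. That value below 80% therefore does not come from omitting them.
- The mean treatment estimate was within 0.005 SD of the truth in every setting, with or without the strata.

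**The case against.** The strongest reply is that this is a condensed article whose full analysis plan is not shown. Covariate lists are often left to such a plan, and the article does not say that baseline is the only adjustment. It is true that the plan may already include the strata. But the article is not silent on covariates: it names one and omits the two randomisation factors. The point is therefore about a stated model that can be improved.

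Several stronger readings are tempting, and the documents do not support them:

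- **That the intervals are certainly too wide.** This depends on gender and residency predicting the outcome beyond its baseline score, and the article does not show that they do.
- **That power falls short of plan because of the omission.** The 74 per group was computed without any adjustment. By the formula, power without the strata is 80.1% or more at every assumed R². Only extra power is forgone.
- **That stratifying becomes pointless.** The balance still lowers the true sampling variance. At R² = 0.10, power without adjustment rises from 80.1% to 81.4%; adjustment would take it to 84.1%. Part of the benefit remains.
- **That the result would be invalid or biased.** The estimate is unbiased, and any error in the test is in the conservative direction.
- **That the same figures apply to the logistic and proportional odds models.** They do not. Adding prognostic covariates to those models changes the odds ratio being estimated and generally does not narrow its standard error, although power can rise. The reference to similar models may also already imply baseline adjustment where a baseline exists.

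**Conclusion.** The mismatch between the stratified randomisation and the stated linear model is real, and its consequence is a modest, conditional loss of efficiency. For an assumed R² of 2% to 10%, intervals are about 1.0% to 5.4% too wide, true alpha is about 4.8% to 3.9%, and about 0.5 to 2.7 points of extra power are forgone. If the factors are not prognostic beyond baseline, nothing is lost. These figures rest on the assumed R², two-sided testing, near-exact balance within strata and a linear model for the 3-month comparison. The sample size, the planned power and the validity of the primary comparison are not in question.

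**What to change.** Before unblinding, state that the linear models for the primary and other continuous outcomes include gender and residency, as randomised, as fixed effects alongside the baseline score.

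For consistency, the same two factors may be added to the logistic and proportional odds models. The plan should then note that the odds ratio is conditional on the strata and that the precision figures above do not apply to it. Perceived change is collected only at 3 and 9 months (Table 3), so it has no baseline score to include.

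The cost is one sentence and two degrees of freedom out of about 148 × 0.85 = 126 evaluable participants. If the factors explain nothing, the simulated intervals widen by about 0.2%. Both variables are known for every participant at randomisation, so no new data are needed. Fixing the covariates in advance also removes later discretion over them.

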### Timelines

Ethics approval was obtained from the Human Research Ethics Committee of the University of Melbourne in August 2013. Recruitment and training of the physiotherapists was completed during February 2014. The trial was registered with the Australian and Zealand Clinical Trials Registry reference: ACTRN12614000243617 in March 2014 prior to participant recruitment which commenced in March 2014 and is expected to be completed by June 2015. The trial is due for completion in March 2016 when all participants are expected to have completed the 9-month follow up.

## Discussion

This paper provides the justification and the protocol for a pragmatic RCT that will investigate whether Internet-based PCST + Ex is more effective than online educational material alone in people with persistent knee pain consistent with a clinical diagnosis of knee OA. The findings of this study will help determine if a PCST and exercise intervention that is delivered using the Internet over 3 months can improve self-reported pain and physical function when compared to an educational control.

Identification of feasible healthcare models that improve outcomes in people with persistent knee pain and knee OA has important implications for clinical practice. Our study will provide new information about the effectiveness and acceptability of a novel clinical practice model for the delivery of interventions that are known to be beneficial to people with persistent knee pain. Findings could therefore have the potential to guide clinical practice towards innovative modes of healthcare provision. This does not diminish the importance of usual methods of delivery of health care, such as face-to-face visits when access is available, however this model could be of particular benefit to people in regional and remote areas who may not be able to access face-to-face care.

In order to maximise translatability, this study was intentionally designed to test a service delivery model that could be easily implemented. Use of a limited number of physiotherapy contacts similar to usual care, a home-based exercise program, and the Internet as a vehicle to deliver the intervention, which is becoming more widely accessible and acceptable to this patient population, will assist this endeavour. If the results of our proposed study support the benefits of Internet-based PCST + Ex, the components of this intervention could be easily implemented into clinical practice.

Strengths of this RCT study design are the pragmatic nature of treatment delivery by practising physiotherapists as well as the reproducibility of both the physiotherapy and pain coping skills programs. These features will improve the ability to translate the findings into a range of health care settings and enable future researchers to replicate the intervention. Importantly, the physiotherapy-guided home exercise program is individualised with regard to the content, and the intensity level of the exercises are individually monitored, progressed or stepped back throughout the intervention according to participant feedback. Additionally, physiotherapists will support and reinforce the participants’ use of the pain coping skills during the exercise sessions so as these skills can not only be integrated into the exercise program, but also encouraged within daily life. The inclusion of participants regardless of their geographic location will further enhance the generalisability of results. The study is adequately powered for our primary outcome measures.

